## Abstract

**Background::**

Acne is a common inflammatory disease of sebaceous glands, which brings extensive emotional and psychological distress to patients. Although acupuncture has certain advantages in the treatment of acne, the curative effect is not exact. The purpose of this trial is to evaluate the feasibility, preliminary efficacy, and safety of the “Spleen and Stomach Guiyuan Acupuncture Method” (SSGA) in the treatment of gastrointestinal damp-heat acne.

**Methods::**

The proposed protocol is planned as a randomized, assessor-blind, conventional-treatment-controlled trial to evaluate the efficacy of SSGA on gastrointestinal damp-heat acne. Seventy six gastrointestinal damp-heat acne patients will be randomly divided into 2 groups and receive SSGA or conventional acupuncture treatment. The entire study period is 12 weeks, including an 8-week treatment period and a 4-week follow-up period. All patients will receive 16 sessions of acupuncture treatment over 8 weeks. The primary outcome is the investigation global assessment (IGA) at week 8, which is an overall assessment of the degree of the inflammatory and non-inflammatory lesion. The secondary outcomes include IGA, the total facial lesion count (Total Lesion Count), the acne-specific quality of life, etc at weeks 8 and 12. The Expectation and Credibility of treatment rating scale will be used to measure the patients’ attitudes to acupuncture after the first treatment. Adverse events will also be recorded.

**Discussion::**

This study is helpful to evaluate the feasibility, preliminary efficacy, and safety of SSGA in the treatment of gastrointestinal damp-heat acne. The results will be used in sample size calculations for subsequent large-scale studies.

Trial registration: Chinese Clinical Trial Registry ChiCTR2100047363. Registered on June 13, 2021.

## Introduction

1

Acne is an inflammatory disease of sebaceous glands common in teenagers,^[1,2]^ mainly caused by hyperkeratosis of hair follicles, increased sebum secretion, and acne bacilli infection in hair follicles.^[3]^ It usually occurs on the face, chest, upper back, and neck, including mild, moderate, and severe. There are different inflammatory lesions at different stages, such as acne, blackheads, pustules, papules, and cystic nodules.^[4]^ Acne is the eighth most prevalent disease in the world, affecting 9.4% of the world's population.^[5]^ It can affect 85% of teenagers,^[1]^ of which moderate to severe accounts for about 20%.^[6]^ A Chinese survey revealed that the prevalence rate in the 19-year-old age group was as high as 46.8%.^[7]^ Though acne was mostly seen in adolescents, it was more common in women than men after the age of 23.^[8–11]^ As a common disease, it has a wide range of potential hazards and related costs. In mild cases, the symptoms are uncomfortable, affect the face, emotional and social psychological distress. In severe cases, they may have emotional and psychological distress, which even causes depression and suicide.^[5]^

At present, most of the treatments for acne are topical and oral retinoic acid, antibiotics and benzoyl peroxide, oral hormones or contraceptives, and so on.^[2]^ These medications generally require a long-term application. Sometimes, the side effects of these drugs are unavoidable, such as the possibility of drug resistance, dryness, peeling, erythema, and skin irritation. Furthermore, the recurrence rate is relatively high after treatment.^[10]^ With the development of medicine in recent years, some non-pharmacological therapies for acne are widely used, such as lasers, light devices including LED device, photodynamic therapy, intense pulsed light, and acupuncture.^[11]^ Acupuncture is widely used to treat various skin diseases.^[12]^ The World Health Organization has recommended acupuncture as an effective treatment for acne.^[13]^ Acupuncture, as a non-pharmacological therapy, has certain advantages in the treatment of acne and has fewer side effects. The existing randomized controlled trials have shown that acupuncture has a certain effect in the treatment of this disease.^[14,15]^ It can not only improve the skin damage of patients with acne but also improve the quality of life.^[16–20]^

However, the existing clinical studies have shown that the curative effect of acupuncture on acne is not exact. The effective rates of different acupuncture treatments are different. Some are relatively high, and some are relatively low. This is because these clinical studies did not adopt the principle of syndrome differentiation and treatment for the therapy of this disease, but only conventional treatment methods.^[16–20]^ The core of Traditional Chinese Medicine (TCM) is syndrome differentiation and treatment. According to the theory of TCM, acne is located in the skin, closely related to the lung, spleen, stomach, and intestine. The basic pathogenesis is heat toxin steaming the skin. The gastrointestinal damp-heat type is the most common in clinical practice. In line with the theory of TCM and clinical experience, the “Spleen and Stomach Guiyuan Acupuncture Method” (SSGA) selects acupoints according to dialectical classification and is mainly used to treat this syndrome. In addition, we found the SSGA is simple and easy to perform, and the effect is good in clinical practice. However, there is no relevant literature to report. Therefore, this trial intends to observe the clinical efficacy of gastrointestinal damp-heat acne through SSGA.

## Materials and methods

2

### Study design and ethics

2.1

The proposed study is a prospective, parallel, two-armed randomized controlled trial using a 1:1 allocation ratio with a 4-week follow-up. The study will be conducted at Dongzhimen Hospital of Beijing University of Chinese Medicine and the Third Affiliated Hospital of Henan University of Traditional Chinese Medicine. The outline of the study patient process is in Figure 1.

**Figure 1 F1:**
[figure not shown]
Flow chart.

The research protocol was approved by the Medical Ethics Committee of Dongzhimen Hospital of Beijing University of Chinese Medicine (2021DZMEC-087-01) and by the Medical Ethics Committee Third Affiliated Hospital of Henan University of Chinese Medicine. We will obtain the patient's informed consent. Study results will be disseminated in peer-reviewed journals, through public events, and relevant third sector organizations.

### Participants

2.2

#### Western medicine diagnostic criteria

2.2.1

Patients with acne will refer to the Chinese Journal of Clinical Dermatology published in April 2017:

1.The age of onset is mostly male and female in adolescence.2.The main affected parts are the face, front chest, and back of the neck.3.The skin lesions are in the form of inflammatory papules, blackheads, whiteheads, pustules, cysts, or dark red nodules. In severe cases, there may even be scars, often accompanied by seborrhea, which is chronic.

#### Diagnostic criteria for gastrointestinal damp-heat type in traditional Chinese medicine

2.2.2

With reference to the “Thirteenth Five-Year Plan” textbook “Traditional Chinese Medicine Surgery,” the diagnostic criteria for gastrointestinal damp-heat acne are as follows:

1.White or blackhead pimples on the face, chest, and back may be accompanied by light yellow or white lipid plugs; or red needle-like papules accompanied by redness and pain; or red papules accompanied by pustules.2.With oily face; or with dry mouth and bad breath.3.Thick stools, yellow urine.4.The tongue is red, the coating is yellow and greasy, and the pulse is slippery.

#### Inclusion criteria

2.2.3

Patients who meet the following conditions will be included:

1.13 to 30 years old, male or female patients with acne.2.Patients meet the diagnostic criteria for acne in Western medicine and the gastrointestinal damp-heat type according to the TCM syndrome differentiation criteria3.Investigation Global Assessment (IGA) score is level 3 (moderate) or level 4 (severe).^[21]^4.Symptoms have been on for more than 6 months.5.Have a certain level of reading comprehension and be able to complete questionnaires independently.6.Patients did not use acne drugs, such as oral, topical, or traditional Chinese medicine, within 4 weeks before entering the group.7.Those who did not participate in other clinical studies within 1 month and were guaranteed not to participate in other clinical studies during this study period.

#### Exclusion criteria

2.2.4

Patients who report the following conditions will be excluded:

1.Pregnant and lactating women, women who have the desire to give birth in the past 2 months.2.Have a history of mental illness.3.Severe liver and kidney dysfunction.4.Cardiovascular, endocrine, hematopoietic system, immune system, and other primary diseases.5.Drug-induced acne and occupational acne.6.Patients who are unwilling to cooperate with acupuncture treatment.7.In the course of treatment, other acne treatments are combined, such as oral or topical treatment with other drugs, laser therapy, and traditional Chinese medicine masks.

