#### Recruitment

2.2.5

Seventy six patients will be recruited through hospital outpatient clinics, advertisements on the hospital's social media (WeChat), and leaflets displayed by community service centers. The recruitment will provide a phone number so that potential patients can contact the researchers. The dermatologist will screen patients who meet the inclusion and exclusion criteria and use a digital camera (Canon EOS 200D) to take facial photos. The study assistant will be responsible for providing study information, such as the objectives, interventions, duration, benefits, and risks. Agreed to participate in the study patients will sign informed consent. The confidentiality of information recorded by patients will be protected.

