#### Randomization and allocation concealment

2.2.6

Patients will be randomly assigned to receive SSGA or conventional acupuncture at a ratio of 1:1. Sealed opaque envelopes will be applied to confirm random hiding. The random sequence number and group assignment information will be sealed in orderly envelopes. With the addition of the patients, these envelopes will be unfolded one by one in order, and the research assistant will record the assigned serial number in the case report form (CRF). The research assistant who does not participate in treatment or evaluation will keep these envelopes.

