#### Blinding

2.2.7

Patients, outcome assessors, and statisticians will turn a blind eye to this assignment. However, due to the characteristics of acupuncture, acupuncturists will not be deceived in this trial. Patients will not know their group status and patients in different treatment groups will be treated in different treatment rooms. Besides, they will be separated by a curtain to avoid communication during the trial. For the successful implementation of blinding, all researchers will be trained before the start of the trial.

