### Intervention

2.3

All patients will receive treatment for 8 weeks, twice a week (every Monday and Thursday), 30 minutes each time, a total of 16 sessions. Acupuncturists will be required to hold a Chinese medicine practitioner license and have more than 1 year of clinical experience. The treatment will use sterile disposable steel needles (Jiajian brand in Wuxi, Jiangsu, China: Suxie Zhuzhun 20152200225). According to the different acupuncture points and the depth of acupuncture, sterile disposable steel needles of different specifications will be selected. And acupuncture will be artificially stimulated for 10 seconds to achieve “Deqi”. That is, the subject will have special sensations such as soreness, numbness, swelling, and weight. And the surgeon has feelings of tightness under the needle.

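### Exclusion item 7 makes other acne treatment during the course a ground for exclusion; applied after randomisation, it opens the comparison to bias of unknown direction and size

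*Protocol article*

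**What the plan says.** Section 2.2.4 (Exclusion criteria) of the protocol article opens with "Patients who report the following conditions will be excluded". Its seventh item reads "In the course of treatment, other acne treatments are combined, such as oral or topical treatment with other drugs", and goes on to list laser therapy and TCM masks.

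Four other places bear on how that item works:

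- **Use before entry** has its own rule, inclusion criterion 6 in section 2.2.3: "Patients did not use acne drugs, such as oral, topical, or traditional Chinese medicine, within 4 weeks before entering the group".
- **Eligibility is checked at recruitment** (section 2.2.5): "The dermatologist will screen patients who meet the inclusion and exclusion criteria".
- **Allocation and treatment come next.** Section 2.2.6 says "Patients will be randomly assigned to receive SSGA or conventional acupuncture at a ratio of 1:1", and section 2.3 says "All patients will receive treatment for 8 weeks, twice a week".
- **The treating staff know the allocation** (section 2.2.7): "due to the characteristics of acupuncture, acupuncturists will not be deceived in this trial".

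The statistical section (2.5.1) does not say what happens to a randomised patient who starts another acne treatment.

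**The concern.** An eligibility criterion has to be decidable before allocation. Adding a drug, laser therapy or a mask during the 8-week course is not. If the rule is followed literally, patients are excluded after randomisation because of something that happened under the assigned treatment.

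That event is unlikely to be independent of outcome. Participants enter with an IGA score of 3 or 4 and no acne drugs in the preceding 4 weeks, so those who are not improving have the most reason to add something. It may also depend on arm, because the acupuncturists are unblinded and see each patient twice a week, so they could influence who is noticed or removed. Excluding such patients would leave two groups that randomisation no longer makes comparable. With 38 patients per arm, a handful of removals is enough to matter.

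**Working it through.** **1. Order of events.** Screening against the criteria (2.2.5) comes before allocation (2.2.6), and allocation comes before the 8-week course (2.3). Item 7 refers to that course, so no patient can meet or fail it at screening on its plain wording. Nor does it simply repeat a baseline rule, since criterion 6 already covers acne drugs in the 4 weeks before entry.

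**2. The plan's own figures (section 2.5.2).** Inputs: effective rate 76.7% for ordinary acupuncture, 98.48% for SSGA, z values 1.645 and 1.282.

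- Difference: 0.9848 − 0.767 = 0.2178.
- n = 0.767 × 0.233 × (2.927 / 0.2178)² = 32.28; the plan states about 32.
- Dropout: 32 × 1.2 = 38.4; the plan states 38, or 76 in total.

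These reproduce. The present point does not depend on them; they supply the rates and arm size for the illustration.

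**3. Effect of removing non-responders.** If the true effective rate is p and a share f of non-responders is removed, the observed rate is

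r(p, f) = p / [p + (1 − p)(1 − f)].

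The documents give no value for f. The values 25% and 50% are assumptions.

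*No true difference, removal from one arm only (p = 0.767 in both arms).* Expected non-responders per arm: 38 × 0.233 = 8.9.

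| f in one arm | Patients removed, of 38 | Rate in that arm | Rate in the other arm | Spurious difference |
|---|---|---|---|---|
| 25% | 2.2 | 0.767 / 0.94175 = 81.4% | 76.7% | 4.7 points |
| 50% | 4.4 | 0.767 / 0.8835 = 86.8% | 76.7% | 10.1 points |

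The sign follows the arm that loses patients: removal from the SSGA arm favours SSGA, and removal from the conventional arm favours conventional acupuncture.

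*Planning rates, same share removed from both arms.*

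| f in both arms | SSGA | Conventional | Difference |
|---|---|---|---|
| 0 | 98.48% | 76.7% | 21.8 points |
| 25% | 0.9848 / 0.9962 = 98.9% | 81.4% | 17.4 points |
| 50% | 0.9848 / 0.9924 = 99.2% | 86.8% | 12.4 points |

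So equal shares do not cancel. At these rates the SSGA arm would have only about 38 × 0.0152 = 0.6 non-responders to lose, and nearly all of the change comes from the conventional arm.

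**4. Scale.** Removing 2 to 4 patients from an arm is within the plan's own allowance for loss, 38 − 32 = 6 per arm.

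**The case against.** Three objections deserve weight.

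**The article does not say that the data are discarded.** Item 7 stands in a recruitment list, and neither the analysis section nor the sample-size section says that a randomised patient who adds treatment leaves follow-up or analysis. The line may be a loosely worded ban on concomitant treatment or a withdrawal rule. This stands. A reader might infer that the plan analyses only patients without added treatment, but the document does not support that. It also names no analysis population, and in a condensed article without its SAP that silence is not a fault. The point is narrower: an exclusion triggered after allocation is printed, and an SAP that kept these patients would have to depart from it.

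**It might be meant as a screening condition.** Inclusion criterion 7 already looks forward, asking for a guarantee of no other study participation during the trial. Exclusion item 7 also names laser therapy, which inclusion criterion 6 does not, so it would not be wholly redundant at entry. This is possible but strains the wording: where the authors want an undertaking they ask for one, and here the trigger is the event itself. It is a reason for moderate rather than high confidence.

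**The size is assumed.** This also stands. The removal shares are not in the documents, and the effective rate comes from the sample-size section, which never links it to the primary outcome, change in IGA score at week 8. A reader might infer that the rule favours SSGA, or that it mostly hides failures in the weaker arm. Neither follows, because both depend on who adds treatment and who is then removed.

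**Conclusion.** The point holds in a limited form, with moderate confidence. A condition that can arise only after randomisation is listed as a ground for exclusion. If it is applied as written, the randomised comparison is open to bias of unknown direction and size.

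The illustrative range is a spurious 4.7 to 10.1 points in either direction when the arms are truly equal, or a fall from 21.8 to between 12.4 and 17.4 points at the planning rates. It rests on three assumptions: that 25% to 50% of non-responders are removed, that no responders are removed, and that the sample-size effective rates are a fair stand-in for response. It shows sensitivity in a trial of this size and does not predict the bias in the IGA analysis. The documents do not show that the comparison will in fact be biased.

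**What to change.** - Move item 7 out of the eligibility list into the trial-conduct text, as a restriction that applies during treatment. Leave unchanged which treatments are allowed. Simply deleting the item would remove the article's only restriction on other acne treatment during the course, which is a clinical matter outside this point.
- State that a breach does not remove a randomised patient from follow-up to week 12 or from the primary analysis.
- Record the start date and type of any other acne treatment in the CRF.
- Analyse all randomised patients as allocated. Report an analysis that leaves out data collected after other treatment starts only as a sensitivity analysis.

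The cost is one relocated line, a sentence or two on analysis, a CRF entry and one small extra analysis. The sample size does not change.

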#### Recruitment

2.2.5

Seventy six patients will be recruited through hospital outpatient clinics, advertisements on the hospital's social media (WeChat), and leaflets displayed by community service centers. The recruitment will provide a phone number so that potential patients can contact the researchers. The dermatologist will screen patients who meet the inclusion and exclusion criteria and use a digital camera (Canon EOS 200D) to take facial photos. The study assistant will be responsible for providing study information, such as the objectives, interventions, duration, benefits, and risks. Agreed to participate in the study patients will sign informed consent. The confidentiality of information recorded by patients will be protected.

#### Randomization and allocation concealment

2.2.6

Patients will be randomly assigned to receive SSGA or conventional acupuncture at a ratio of 1:1. Sealed opaque envelopes will be applied to confirm random hiding. The random sequence number and group assignment information will be sealed in orderly envelopes. With the addition of the patients, these envelopes will be unfolded one by one in order, and the research assistant will record the assigned serial number in the case report form (CRF). The research assistant who does not participate in treatment or evaluation will keep these envelopes.

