#### Sample size

2.5.2

The total sample size was 76 cases and they are randomly divided into 2 groups. According to the trial design, the sample size estimation method used a completely random design sample rate and the population rate comparison. The sample size is calculated according to the following formula: $\text{n}=\pi_{0}\left(1-\pi_{0}\right){\left\{\frac{{\text{z}}_{\alpha }+{\text{z}}_{\beta }}{\delta }\right\}}^{2}$. Through literature study on ordinary acupuncture treatment for acne patients, the average effective rate was 76.7%, so the overall rate of Group A was *π*_0_ = 76.7%. Combined with clinical experience, the total effective rate of SSGA in treating acne is 98.48%, then the overall rate of expected test results was *π* = 98.48%. One-sided cutoff of this trial: z_α_ = 1.645, z_β_ = 1.282, δ=*π*-*π*_0_ = 0.9848-0.767 = 0.2178. Enter the formula to get the estimated sample content value n≈32. Considering that “dropping” may increase the sample size by up to 20%, the sample size was estimated to be 38 cases. Finally, Group A and Group B are according to the random number table method.

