## Discussion

3

Acne is a chronic inflammatory skin disease, and its pathogenesis is still not completely clear. Modern studies suggest that its onset is related to the relative increase of androgens, increased secretion of sebum, hair follicles mouth of excessive and Propionibacterium acnes infection and so on. In addition, the immune imbalance, the role of inflammatory factors, and genetic related factors have also been recognized.^[11]^ The general effects of acne are physical sensory symptoms such as skin itching and pain. However, the most serious impact is on the quality of life. This influence is affected by various factors, which makes it difficult to quantitatively analyze. In youth, the self-confidence and self-esteem of acne sufferers are affected. If it can’t be cured, it may bring continuous negative psychological effects on adults, such as shame, embarrassment, depression, anxiety, and even suicide. Therefore, complementary and alternative medicine in modern practice regarding various dermatology is becoming more and more extensive.

As a unique alternative treatment method, acupuncture has the function of “external treatment of internal diseases” and can treat systemic diseases through the conduction of meridians and acupoints.^[25]^ It is widely used in China and has achieved good results in the treatment of acne, chloasma, eczema, allergic skin diseases, and other skin diseases.^[13]^ However, the existing trials only provide routine treatment for this disease and do not conduct syndrome differentiation.^[26–30]^ TCM treats acne and adopts the principle of syndrome differentiation and treatment. Starting from the origin, the advantages are significant.^[31,32]^ Therefore, under the guidance of TCM theory and clinical experience, we have designed a study on acne with the gastrointestinal damp-heat syndrome. This trial is based on the guidance of TCM theory. We aim to evaluate the changes in the count of facial skin lesions and the improvement of quality of life in patients with acne by SSGA. This study is a multi-center clinical randomized trial, which is more in line with clinical practice and closer to the real world. Moreover, the selection of acupoints is within a relatively safe range of the lower limbs, avoiding operations on the local lesions, so the patients’ acceptance is relatively high.

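### Allocation in a two-hospital trial is described with no blocked or separate list per hospital, and the primary test adjusts for neither hospital nor baseline IGA

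*Protocol article*

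**What the plan says.** Study design and ethics (2.1) names two hospitals and describes a "parallel, two-armed randomized controlled trial using a 1:1 allocation ratio". The Discussion states: "This study is a multi-center clinical randomized trial".

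Randomization and allocation concealment (2.2.6) repeats the ratio: "Patients will be randomly assigned to receive SSGA or conventional acupuncture at a ratio of 1:1". Sequence number and group are sealed in ordered envelopes. A research assistant outside treatment and evaluation keeps them, and as patients join "these envelopes will be unfolded one by one in order".

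Sample size (2.5.2) gives the size, "The total sample size was 76 cases and they are randomly divided into 2 groups", and the method of generation: "Finally, Group A and Group B are according to the random number table method". It labels the design in these words: "the sample size estimation method used a completely random design sample rate and the population rate comparison".

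None of these sections mentions a block, a stratum, a list for each hospital or central allocation.

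Inclusion criteria (2.2.3) admit IGA grades 3 and 4 only. Primary outcome (2.4.1) defines the outcome as the change in IGA from baseline to week 8. Clinical data analysis (2.5.1) compares the week-8 IGA between groups by a chi-square test, with no covariate.

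**The concern.** The article sets out an allocation procedure, but the procedure takes no account of there being two hospitals. Hospital could plausibly affect the result. Acupuncture depends on the operator, the acupuncturists are unblinded, and the primary outcome is a global grade given by an assessor. Baseline grade could plausibly matter too, because a patient who starts at grade 4 has further to fall than one who starts at grade 3.

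If the arms differ by chance in their mix of hospitals or baseline grades, part of the observed difference in week-8 IGA belongs to that mix. With 76 patients such differences are not rare. An unadjusted chi-square test has no means of separating the two. The trial would then report a preliminary effect, meant to inform the size of a later study, that is less precise than its own data allow and open to an obvious challenge.

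**Working it through.** **Inputs from the article.** Total 76, ratio 1:1, two hospitals (2.1, 2.2.6, 2.5.2). Baseline IGA 3 or 4 (2.2.3). Control rate 0.767, SSGA rate 0.9848, z-values 1.645 and 1.282, increase for dropout up to 20% (2.5.2).

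**Assumptions.** The number of patients per hospital is not given; I use 38, 26, 20 and 16 for one of the two. The share of patients at grade 4 is not given; I use one half.

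**Step 1. The plan's own figure.** n = 0.767 × 0.233 × ((1.645 + 1.282) / 0.2178)² = 32.28, stated as about 32. Then 32 × 1.2 = 38.4, stated as 38 per group, so 76 in total. Both figures reproduce.

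**Step 2. Overall split if the table is used patient by patient.** The size of group A is Binomial(76, 0.5).
- Exactly 38:38: C(76,38) / 2⁷⁶ = 9.1%.
- 43:33 or worse (a difference of 10 or more): 30.2%.

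If the table was instead used to fill two groups of exactly 38, the overall split is fixed at full enrolment and these figures do not apply.

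**Step 3. Split within one hospital.** With a list fixed at 38:38 and m patients at one hospital, the number in group A there is hypergeometric: P(k) = C(38,k) × C(38,m−k) / C(76,m). With unrestricted allocation it is Binomial(m, 0.5). The probability of 60:40 or worse is:

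| Hospital size m (assumed) | Smallest split counted | Fixed 38:38 list | Unrestricted |
|---|---|---|---|
| 38 | 23:15 | 10.8% | 25.6% |
| 26 | 16:10 | 22.6% | 32.7% |
| 20 | 12:8 | 43.5% | 50.3% |
| 16 | 10:6 | 39.9% | 45.4% |

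The value at 16 is below that at 20 because whole patients make 10:6 a stricter split (62.5%) than 12:8 (60%).

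**Step 4. What such a split does to the comparison.** With 38 per arm, the arms differ in the share from that hospital by (kA − kB) / 38:
- 23:15 gives 8/38 = 21 points.
- 16:10 gives 6/38 = 16 points.
- 12:8 and 10:6 give 4/38 = 10.5 points.

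For every 10 points by which the hospitals differ in success rate, the unadjusted arm difference shifts by about 2.1, 1.6 or 1.1 points. The planned difference is 21.78 points. The splits that arise most often, in a small hospital, shift the result least.

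**Step 5. Baseline grade.** With 38 per arm and half the patients at grade 4, the difference in counts has the same distribution as in Step 2. A gap above 10 points needs at least 4 patients (4/38 = 10.5%) and has probability 42.2%. A gap above 15 points needs at least 6 patients (6/38 = 15.8%) and has probability 20.7%.

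**Step 6. Power.** On the planned rates, two-sided 5% power is 83.5% at 38:38. At 46:30 it is 79.7% or 84.1%, depending on which arm is smaller. Overall imbalance therefore costs at most about 4 points of power.

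**The case against.** The strongest reply is that simple randomisation is valid. A chance imbalance is already allowed for in the error rate of the test, so nothing here is biased. That stands. The point concerns precision and a credible estimate.

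A reader might infer that one envelope series is shared by both hospitals and so cannot be opened in order at both. The article does not support this. It does not say that there is only one series or where the envelopes are kept. One keeper could open a single series as patients enrol and relay the assignment, or each hospital could hold its own set.

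A reader might also infer that 1:1 fails overall. That depends on how the table is used. If it fills two groups of 38, overall balance holds at full enrolment, and even a poor overall split costs little power.

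The absence of stratification by IGA grade might be read as an error. At 76 patients it is a preference, and adjustment in the analysis does much of the same work. The article also gives no figure for the effect of baseline grade or of hospital, and it does not say that staff differ between hospitals. Defining the primary outcome as change from baseline would deal with part of the baseline difference, but the stated test uses the week-8 score, and a change score would leave hospital untouched.

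Finally, a condensed article may leave block sizes and list logistics to the full protocol. That is fair for the details. It does not cover the primary test, which the article fixes as unadjusted, nor the method of generation, which it states with no restriction.

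**Conclusion.** The point holds as a design weakness that should be corrected; it is not an error that invalidates the trial. As described, allocation does not secure balance within hospital: 60:40 or worse in one hospital in about 11% to 44% of allocations with a fixed 38:38 list, for assumed hospital sizes of 38 to 16. Overall 1:1 is unsecured only if the table is used patient by patient (30% chance of 43:33 or worse). The stated primary test cannot account for either hospital or baseline IGA.

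The effect on the result depends on how far outcomes differ by hospital and by baseline grade, which the article does not tell us. On the figures above, the shift from hospital alone is about 1 to 2 points per 10 points of difference between hospitals.

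**What to change.** 1. **Allocation.** Generate a separate permuted-block list for each hospital, with varying block sizes not disclosed to the sites, and give each hospital its own numbered envelope set. State who holds each set. Stratifying further by baseline IGA is optional; four lists would average 76 / 4 = 19 patients each and leave more incomplete blocks.
2. **Analysis.** Replace the unadjusted chi-square test with a model for week-8 IGA that includes arm, hospital and baseline IGA (3 or 4), for example ordinal logistic regression. Say in advance how sparsely filled grades will be combined.

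The cost is a new list before enrolment and slightly more envelope administration. No further patients or staff are needed, and baseline IGA is already collected. One drawback is that assignments near the end of a block become somewhat more predictable because the acupuncturists are unblinded; varying, undisclosed block sizes reduce this but do not remove it. If enrolment has already begun, the second change can still be made before the data are unblinded.
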